16.4 Exploratory endpoints

16.4.1 Archived tissue collected from biopsy of enrolled patients will be sent for pathological assessment of cellular and genetic mutations to correlate them with disease local relapse and radiation resistance, where applicable. This includes:

16.4.1.1 TP53 gene alteration by Fluorescence in situ hybridization (FISH)

16.4.1.2 Expression of TP53, MYC and proliferation index (Ki-67) by immunohistochemistry stain (IHC)

16.4.2 Baseline PET/CT scan of patients will be sent to MIMvista to undergo autosegmentation to calculate the MTV, TLG and SUVmax of their disease to correlate it with disease local relapse and treatment response.

16.4.3 Financial toxicity: financial side effects induced by cancer treatment that will be assessed by a modified COST-FACIT questionnaire as outlined in section 4.0 and 7.0.

16.4.4 Financial health care expenditure reflects the costs spent on health care and related activities attributable to this cancer treatment and will be assessed as outlined in section 4.0 and 7.0.

16.4.5 Sensitivity analysis to assess differences in the different radiation dose regimens in the experimental treatment arm.

### 16.5 Statistical Design

16.5.1 Decision Rules

16.5.1.1 A two group χ^2^ test of equal proportions in acute adverse events will be conducted to determine the efficacy in acute toxicity reduction within the treatment arm. If the p-value of the statistical test is less than 0.10 then the treatments will be considered significantly different in the direction of the point estimates. Therefore, a significant difference in the direction of the experimental arm will deem the treatment favorable and worth consideration in future trials. If the test is non-significant then the experimental arm will not be considered significantly different in toxicity profile and therefore, not considered for future trials. It is also important to consider the local control rate when deciding whether to pursue further study. In the FoRT trial, the 2-year local progression-free rate was 94.1% after 24 Gy and 79.8% after 4 Gy. If the observed 2-year probability of local control is more than 7% inferior with 9 Gy versus 24 Gy, then we will not consider future trials. For example, if the 2-year local control rate is 94.1% after 24 Gy, and less than 87.1% after 9 Gy then we would not pursue further study.

16.5.1.2 Over Accrual: We will accrue approximately 10% over-accrual (112 total patients, 56 per arm) in order to ensure 102 evaluable patients as described in previous sections. The first 102 evaluable patients will be utilized for analysis of the primary endpoint.

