## **4.0 Test Schedule**

|  |  | **Active Monitoring Phase** | | | **Clinical Follow-Up** | | |
| --- | --- | --- | --- | --- | --- | --- | --- |
| **Tests and procedures** | ***≤ 45 days prior to registration*** | ***End of Treatment*** | ***Day 7***  ***post-ISRT*** | ***Day 14***  ***post-ISRT*** | ***3 Months***  ***post-RT^1^*** | ***6 Months***  ***post-RT*** | ***Every clinically indicated follow-up***  ***(q 6 months)^1^*** |
| Window |  | ±1 day | ±2 days | ±2 days | ±14 days | ±30 days | ±30 days |
| History and exam, PS^2^ | X |  |  |  | X | X | X |
| Radiation Oncology consult^2^ | X |  |  |  |  |  |  |
| Adverse Event assessment^3^ | X | X | X | X | X |  |  |
| Pregnancy test^2,^4 | X |  |  |  |  |  |  |
| Hematology group: CBC with 5-part differential  (HgB, WBC, PLT, LDH)^2^ | X |  |  |  |  |  |  |
| PET/CT ^2^ | X  (90 days) |  |  |  | X  (strongly consider, unless FDG negative at baseline) | X* | X* |
| CT Chest/Abdomen/Pelvis +/- Neck^2, 7^ |  |  |  |  | X  (if PET not done) | X* | X* |
| Endoscopy with gastric biopsy (only if gastric lymphoma)^2^ | X  (***≤*** 90 days) |  |  |  | X^6^ | X** |  |
| Patient Reported Outcomes (Appendix II: FACIT-Fatigue)^3^ | X | X | X |  | X |  |  |
| Financial Toxicity Questionnaire  (Appendix II: COST-FACIT)^3^ |  | X |  |  |  |  |  |
| Optional Research,  tissue specimen5^,R^ |  | X |  |  |  |  |  |

Radiation treatment (RT) = 3 vs. 12 fractions (5 days vs. 16 days ±2 days)

^1^ Follow-up assessments will be completed as per clinician’s discretion.

^2^ Standard of care

^3^ Research non-billable

^4^ For persons of childbearing potential only. Must be done ≤7 days prior to registration.

^5^ Historic tissue specimen may be pulled and used for analysis by end of study.

^6^ +/- 30 days

^7^ CT and/or PET should not be mandated for patients with primary cutaneous lymphoma where physical exam is used for evaluation of treatment response..

^R^ Research funded

* CT chest/abdomen/pelvis +/- neck or PET/CT or PET/MRI ok at these time points

** If 3 month biopsy was positive

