13.4 Inevaluable patients

If a patient fails to complete Radiation Therapy for reasons other than toxicity, the patient will be regarded as unevaluable.

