### 16.2 Primary endpoints

The following definition is used for the primary endpoint of interest:

- Acute toxicity: any adverse event grade 2 or higher (CTCAE v5.0) possibly related to radiation treatment, reported at End of Treatment, Day 7 post RT, or Day 14 post RT. Acute toxicity is reported as a proportion calculated as the number of patients with acute toxicity divided by the total number of treated patients.

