16.5.2 Sample Size

102 evaluable patients will be accrued to this phase-II study unless undue toxicity is encountered. We anticipate accruing an additional 10 patients to account for ineligibility, cancellation, major treatment violation, or other reasons. Maximum projected accrual is therefore 112 patients.

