16.6 Analysis Plan

The primary analysis for this trial will commence once the first 102 evaluable patients have completed their Day 14 Post ISRT visit. It is anticipated that the earliest date in which the results will be made available via a manuscript, abstract, or presentation format is when 102 patients have experienced an acute toxicity or 2 weeks post radiation therapy follow-up.

16.6.1 Primary Analysis: The primary analysis will be to compare the proportion of patients who experience an acute toxicity within the first 2 weeks of finishing RT between the 2 treatment arms.

16.6.1.1 Acute toxicity: All patients who were registered to the study and started treatment will be included in the acute toxicity analysis. Acute toxicity has been defined in section 16.2. A chi-squared test will be used to compare acute toxicity rates between treatment arms. A two-sided p-value less than 0.10 will be considered statistically significant (see decision rule). To assess the size of differences, absolute risk difference and relative risk will be calculated; 95% confidence intervals will be calculated using the score method. Although we will use an alpha of 0.10 for deciding whether to pursue further study, 95% confidence intervals will be reported for estimates for ease of interpretation.

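### The protocol names two incompatible sets for the primary toxicity test: the first 102 evaluable patients, and all patients who started treatment

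*Protocol*

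**What the plan says.** Two sets are given for the same test.

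- **Evaluable set.** Section 16.5.1.2: "The first 102 evaluable patients will be utilized for analysis of the primary endpoint". The opening of 16.6 agrees: "The primary analysis for this trial will commence once the first 102 evaluable patients have completed their Day 14 Post ISRT visit".
- **Treated set.** Section 16.6.1.1: "All patients who were registered to the study and started treatment will be included in the acute toxicity analysis". Section 16.2 defines the endpoint as "the number of patients with acute toxicity divided by the total number of treated patients".

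Evaluability is defined mainly by what removes it. Section 13.4: "If a patient fails to complete Radiation Therapy for reasons other than toxicity, the patient will be regarded as unevaluable". Section 16.5.2 explains the over-accrual: "We anticipate accruing an additional 10 patients to account for ineligibility, cancellation, major treatment violation, or other reasons". Sections 13.5 and 13.6 show that ineligible patients and major violators may nevertheless have been treated.

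The test is a chi-squared test at two-sided 0.10, and 16.5.1.1 ties the decision on future trials to it.

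**The concern.** Two analysts who both follow the protocol could run different primary tests. A patient who starts radiotherapy and stops for, say, a travel reason is in the treated set and out of the evaluable one. A patient treated after the 102nd evaluable patient is likewise in one and out of the other, although the Day 14 outcome will be known.

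The evaluable version is also the weaker of the two. Its exclusion happens after randomisation and depends on a judgement of why treatment stopped. The protocol describes no blinding, and the arms differ visibly in number of fractions. Because the endpoint is itself toxicity, deciding that a stop was not due to toxicity lies close to the outcome. At stake is which result is read against the 0.10 threshold.

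**Working it through.** **1. The plan's own power.** Inputs from 16.5.4: 0.31 v 0.10, two-sided alpha 0.10, 51 per arm, stated power 80%. Exact enumeration gives 79.1% for the continuity-corrected chi-squared or Fisher test, which reproduces the stated figure. For the uncorrected test, by normal approximation:

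- Power = Φ[(0.21 − 1.645·s0)/s1], with s0 = √(2·0.205·0.795/n) and s1 = √((0.31·0.69 + 0.10·0.90)/n).
- n = 51: s0 = 0.0799, s1 = 0.0772, z = 1.017, power 84.5%.
- n = 56: s0 = 0.0763, s1 = 0.0737, z = 1.147, power 87.4%.

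The corrected or Fisher figure at 56 per arm is 83.3%. All figures at 56 per arm assume that all 112 patients are treated and analysed, so they are upper limits.

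**2. How many patients separate the sets.** The cap can leave out at most 112 − 102 = 10 accrued patients. Non-completion is not quantified in the protocol. Section 4.0 gives only the course lengths: "Radiation treatment (RT) = 3 vs. 12 fractions (5 days vs. 16 days ±2 days". As an assumption, let h be the chance per fraction of stopping for a non-toxicity reason, equal in both arms. Then non-completion = 1 − (1 − h)^k for k fractions:

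| h | 3 fractions | 12 fractions |
|---|---|---|
| 0.2% | 0.6% | 2.4% |
| 0.5% | 1.5% | 5.8% |
| 1% | 3.0% | 11.4% |

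Under this assumption the 12-fraction arm loses about four times as many.

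**3. Effect on the estimate.** Take 56 per arm, a true difference of 0.21 among all treated, and m non-completers dropped from the 24 Gy arm only, a proportion e of whom had an event. The remaining control rate is (0.31·56 − m·e)/(56 − m).

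- m = 3: the difference is 0.171 if all had events, 0.228 if none had.
- m = 5: the difference is 0.142 to 0.240.

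So the shift can go either way.

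**4. Effect on the decision.** Uncorrected chi-squared, X² = N(ad − bc)²/(product of the four margins); illustrative counts.

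- 17/56 v 8/56: 112·504²/(56·56·25·87) = 4.171, p = 0.041.
- Drop three controls, all with events, 14/53 v 8/56: 109·360²/(53·56·22·87) = 2.487, p = 0.115.
- Drop three controls of whom two, one or none had events (15/53, 16/53, 17/53 v 8/56): p = 0.073, 0.045, 0.027. The decision is unchanged.
- 15/56 v 8/56: X² = 2.681, p = 0.102. Drop two event-free controls, 15/54 v 8/56: X² = 3.026, p = 0.082. Here the exclusion creates significance.

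If events were independent of stopping, the chance that all three dropped controls had events is 17/56 × 16/55 × 15/54 = 2.5%.

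These crossings depend on the test variant. With continuity correction the first example still crosses (0.069 to 0.181). The reverse one does not (0.160 to 0.132).

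**The case against.** The best defence is that 16.6.1.1, the section devoted to this analysis, plainly includes everyone who started treatment. On that reading 102 is a planning number and a trigger, and 13.4 does not say for which endpoint a patient is unevaluable. That reading is sensible, but 16.5.1.2 says the 102 are the patients used for the primary analysis, so the text does not allow it without an edit.

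A reader might infer that the evaluable set is known to lose more control patients and so biases the comparison in a known direction. The documents do not support this. Differential loss is inferred from course length alone, patients who stop for toxicity are kept, and step 3 shows shifts both ways.

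A reader might also infer that the decision is likely to change. It is not. The three-event case is an extreme, and at about the design rates it does not change the result: 17/56 v 6/56 gives p = 0.010, and 14/53 v 6/56 gives p = 0.034.

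Nor is the rise to 87.4% a promised gain. The extra 10 patients are there to cover losses, and cancelled patients (13.7) never receive a fraction. If attrition runs as planned, few evaluable patients fall beyond the 102nd.

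Finally, a set of patients with at least one fraction still omits those randomised but never treated. That is a real limit. It is, however, the set that 16.2 and 16.6.1.1 already choose for a treatment-toxicity endpoint.

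**Conclusion.** The contradiction stands and needs correcting before outcomes are examined. The protocol states the primary set twice, differently, for the test that drives the go/no-go decision. This is a conflict in stated rules, not detail left for an analysis plan.

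The practical size is modest. At most about 10 patients are affected by the cap, and an unknown, probably small, number by 13.4. In borderline data two or three patients are enough to move p across 0.10, in either direction. More frequent exclusion in the 12-fraction arm is a reasonable expectation that rests on the assumed equal chance of stopping per fraction. It is not something the protocol establishes.

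**What to change.** - In 16.5.1.2, delete the sentence "The first 102 evaluable patients will be utilized for analysis of the primary endpoint" and keep 102 as the planning number only.
- In the opening of 16.6, align the trigger so that the analysis starts when all enrolled and treated patients have reached Day 14.
- In 16.6.1.1, name one primary set: all randomised patients who received at least one fraction, analysed in the assigned arm, whether or not radiotherapy was completed.
- In 13.4, state that this classification removes no one from the acute toxicity analysis.
- Report the evaluable set as a sensitivity analysis.

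The cost is a few sentences in an amendment and a short wait for the last enrolled patients. Power is not reduced relative to 51 per arm, provided that at least 102 patients are treated and assessed.

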16.5.2 Sample Size

102 evaluable patients will be accrued to this phase-II study unless undue toxicity is encountered. We anticipate accruing an additional 10 patients to account for ineligibility, cancellation, major treatment violation, or other reasons. Maximum projected accrual is therefore 112 patients.

16.5.3 Accrual Time and Study Duration

We anticipate enrolling 112 patients and thus plan to finish accrual of patients in 1.5-2 years after opening the study. Therefore, the overall study duration is expected to be 48 months.

16.5.4 Power and Significance Levels

The study is designed as a two arm 1:1 randomized Phase II trial with a total evaluable sample size of 102 patients and a 1:1 randomization (51 patients per arm). We will utilize a two-group chi-squared test of equal proportions with a two-sided α = 0.10 to test the primary hypothesis given acute toxicity estimates observed in the FoRT trial (grade 2+ acute toxicity of approximately 31% in the 24 Gy arm and approximately 9% in the 4 Gy arm). We hypothesize similar estimates in the 24 Gy arm, and we hypothesize acute toxicity rates of 10% in the 9 Gy arm. With a two-sided alpha of 0.10 we will achieve 80% power to detect difference in proportions of 0.21 when the acute toxicity is assumed to be 0.31 in the standard of care arm and 0.10 in the experimental arm. To ensure evaluability of our primary endpoint we will accrue 10 additional patients (56 per arm) to account for approximately 10% lost to follow-up.

16.5.5 Other Considerations

Adverse events observed in this study as well as scientific discoveries or changes in standard care will be taken into account in any decision to terminate the study.

16.6 Analysis Plan

The primary analysis for this trial will commence once the first 102 evaluable patients have completed their Day 14 Post ISRT visit. It is anticipated that the earliest date in which the results will be made available via a manuscript, abstract, or presentation format is when 102 patients have experienced an acute toxicity or 2 weeks post radiation therapy follow-up.

16.6.1 Primary Analysis: The primary analysis will be to compare the proportion of patients who experience an acute toxicity within the first 2 weeks of finishing RT between the 2 treatment arms.

16.6.1.1 Acute toxicity: All patients who were registered to the study and started treatment will be included in the acute toxicity analysis. Acute toxicity has been defined in section 16.2. A chi-squared test will be used to compare acute toxicity rates between treatment arms. A two-sided p-value less than 0.10 will be considered statistically significant (see decision rule). To assess the size of differences, absolute risk difference and relative risk will be calculated; 95% confidence intervals will be calculated using the score method. Although we will use an alpha of 0.10 for deciding whether to pursue further study, 95% confidence intervals will be reported for estimates for ease of interpretation.

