## **5.0** **Stratification Factors OR Grouping Factors**

Stage I/II vs. Stage III/IV/relapse/refractory

Enrollment site (FL, AZ, MN)

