### 6.2 Randomization Procedures

#### 6.2.1 The factors defined in **Section 5.0** will be used as stratification factors.

#### 6.2.2 After the patient has been registered into the study, the values of the stratification factors will be recorded, and the patient will be assigned to one of the following treatment groups using the Pocock and Simon dynamic allocation procedure, which balances the marginal distributions of the stratification factors between the treatment groups (Pocock and Simon 1975).

- Arm 1: The prescription dose will be 9 Gy delivered in 3 fractions of 3 Gy per fraction or 8 Gy delivered in 2 fractions of 4 Gy per fraction . In some cases, the investigator can use 10 Gy delivered in 5 fractions (stomach/orbit/other at treating MD’s discretion).
- Arm 2: The prescription dose will be 24 Gy delivered in 12 fractions of 2 Gy per fraction.

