16.6.2 Secondary Analyses

16.6.2.1 Response Rate: All patients who were registered to the study and started treatment will be included in the response rate analysis. Response rate will be defined as the proportion of patients displaying response (PR or CR) at 3 months post treatment; patients who did not have a 3-month post treatment assessment will be considered a non-response. A chi-square test will be used to compare response rates between the two treatment arms. Absolute risk difference and relative risk will be calculated; 95% confidence intervals will be calculated using the score method.

16.6.2.2 Local control: All patients who were registered to the study and started treatment will be included in the local control analysis. A local recurrence event is any event defined as disease relapse occurring in the area treated before with radiation (anything included within the 95% isodose line). The local control interval will be defined as the number of days from end of radiation treatment until first local recurrence within 24 months post radiation treatment; censoring will occur at date of patient death or date of last disease evaluation (based on imaging and clinical exam). Local control rates will be estimated separately for the two treatment groups at 3-, 6-, 12-, 18, and 24-months post radiation treatment using the Kaplan-Meier method. Hazard ratio and 95% confidence interval for comparison of local recurrence between the two treatment arms will be estimated from a Cox proportional hazards model.

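### Allocation is minimised on stage group and site, but the acute-toxicity and response comparisons are fixed as unstratified chi-square tests, which are conservative if those factors are prognostic

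*Protocol*

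**What the plan says.** Protocol 5.0 names two stratification factors: stage group ("Stage I/II vs. Stage III/IV/relapse/refractory") and site ("Enrollment site (FL, AZ, MN"). Protocol 6.2.2 uses both in the "Pocock and Simon dynamic allocation procedure, which balances the marginal distributions of the stratification factors between the treatment groups".

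The primary comparison is fixed without these factors in three places. The decision rule (16.5.1.1) is a two-group chi-square test of equal proportions with a p<0.10 threshold. The power section (16.5.4) says "We will utilize a two-group chi-squared test of equal proportions with a two-sided α = 0.10". The analysis section (16.6.1.1) says "A chi-squared test will be used to compare acute toxicity rates between treatment arms", and adds that "absolute risk difference and relative risk will be calculated; 95% confidence intervals will be calculated using the score method". Response at three months (16.6.2.1) has the same form: "A chi-square test will be used to compare response rates between the two treatment arms".

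No section brings stage group or site into either comparison. The only covariate adjustment is in the exploratory biomarker models (16.6.2.5), which do not name these factors.

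**The concern.** Minimisation limits chance imbalance between arms in stage group and site. The crude chi-square variance is computed as if that imbalance were still free to occur. If the factors predict toxicity or response, the variance is too large, so the p-value and the interval are wider than the design warrants.

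This matters mainly at the primary test. Under 16.5.1.1, a non-significant result means that the experimental arm is not taken forward. A needlessly conservative test at that gate works against the trial's own aim. The point cannot simply be left to a SAP. The protocol already names the test, the alpha, the effect measures and the interval method, and a two-group chi-square test cannot carry strata. A stratified test in a SAP would contradict the protocol.

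**Working it through.** **Inputs from the protocol.** 102 evaluable patients, 51 per arm; two-sided alpha 0.10; rates 0.31 v 0.10; stated power 80% (16.5.4). Two stage groups and three sites (5.0).

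**Inputs assumed, because the documents give none.** Stage split 50/50; sites 50/25/25; biased-coin probability 0.8; stage and site effects as odds ratios (OR), with site as an OR per step.

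**1. The plan's own power.** The mean rate is (0.31 + 0.10)/2 = 0.205. By the normal approximation:

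z = [0.21·√51 − 1.645·√(2·0.205·0.795)] / √(0.31·0.69 + 0.10·0.90) = (1.500 − 0.939)/0.551 = 1.017, so power is 84.5%.

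Exact enumeration gives 85.8% for the uncorrected Pearson test and 79.1% for the continuity-corrected or Fisher test. The stated 80% is therefore reproduced by the corrected variant and exceeded by the uncorrected one.

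**2. Why the crude test is conservative, in closed form.** If the strata were perfectly balanced, the variance of the crude statistic would shrink by 1 − R², where R² = Var(stratum rates)/[p(1 − p)]. The true null rejection would be 2·[1 − Φ(1.645/√(1 − R²))]. With a common rate of 0.31, p(1 − p) = 0.2139.

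- Stage OR 2, site OR 1.5: between-stratum variance 0.0102, R² = 0.048, rejection 9.2%.
- Stage OR 3, site OR 2: 0.0252, R² = 0.118, rejection 8.0%.
- Stage OR 5, site OR 2.5: 0.0423, R² = 0.198; 1.645/√0.802 = 1.837; rejection 6.6%.

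These are limits. Minimisation balances the margins and not every cell, so the real shortfall should be smaller.

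**3. Simulation of the actual allocation.** Pearson chi-square v Cochran-Mantel-Haenszel (CMH) over the six stage-by-site strata, both without continuity correction, 8,000 to 20,000 trials per scenario (Monte Carlo error about 0.2 to 0.4 points):

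| Assumed effects (stage OR / site OR) | Null rejection, common rate 0.31: crude v CMH | Null rejection, common rate 0.205: crude v CMH | Power, 0.31 v 0.10: crude v CMH |
|---|---|---|---|
| none | 10.0% v 9.7% | 10.5% v 10.1% | 86.2% v 85.3% |
| 1.5 / 1.25 | 10.2% v 10.0% | 10.1% v 10.2% | 86.2% v 85.5% |
| 2 / 1.5 | 9.5% v 9.9% | 10.4% v 10.3% | 86.1% v 86.0% |
| 3 / 2 | 8.5% v 10.1% | 9.1% v 10.7% | 87.7% v 88.2% |
| 5 / 2.5 | 7.8% v 10.6% | 8.3% v 10.4% | 87.6% v 89.4% |

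A second run with a biased coin of 0.9 (5,000 trials per scenario, common rate 0.31) gave crude null rejection of 9.8%, 8.1% and 7.7% in the last three scenarios, against 10.7%, 10.0% and 10.4% for CMH.

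**4. Sparseness.** Expected events at the design rates are 51 × 0.31 + 51 × 0.10 = 20.9, or about 3.5 per cell over six cells. In simulation at the design alternative, at least one cell contributed nothing to the CMH statistic in 22-35% of trials.

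**5. Response.** The protocol gives no planning rates for response, so no size was computed there. The same reasoning about direction applies.

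**The case against.** The case for leaving the plan alone is reasonable. The three sections on the primary test agree with each other, the sample size was calculated for that test, and nothing in the protocol promises a stratified analysis. There is no internal contradiction and no inflation of false positives. The documents give no evidence that stage group or site predicts acute toxicity. If neither does, CMH loses 0.9 points of power (85.3% v 86.2%). Six cells with about 21 events are sparse, and a continuity-corrected CMH had power of only about 78-82%. All of this stands. It limits the size of the point and shapes the fix, but the mismatch between allocation and analysis remains.

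Three stronger readings are tempting, and the documents do not support them:

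- **That the primary test fails to hold its 10% level.** A test that rejects 8-9% of the time under the null still controls type I error at 10%. It is conservative, and only under assumed prognostic effects.
- **That stratifying is free.** It costs up to about 1 point of power if the factors do not matter.
- **That the local-control Cox model is unadjusted.** Section 16.6.2.2 names a Cox model for the arm comparison and is silent on covariates and strata. A SAP may properly specify them.

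**Conclusion.** The point holds as a modest mismatch between allocation and analysis in the primary and response tests. Type I error is protected and the sample size stands. If stage group and site are prognostic, the crude test is conservative: at a common rate of 31%, null rejection is about 9% with moderate effects and 7-8% with strong effects, against the nominal 10%. At a common rate of 20.5% the shortfall is smaller. Stratifying changes power by about -1 point (factors irrelevant) to about +2 points (factors strong). In every scenario the uncorrected CMH test kept power above 85%, so the stated 80% is not at risk.

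The size rests on assumed stage and site splits, an assumed biased-coin probability and assumed odds ratios. The direction does not depend on the particular values chosen, provided the factors are prognostic.

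**What to change.** In 16.6.1.1, make the primary test a Cochran-Mantel-Haenszel test stratified by stage group and site, without continuity correction, at two-sided 0.10. Report the Mantel-Haenszel risk difference and relative risk with 95% intervals. State in advance how a sparse cell is recognised, and that sites are then pooled within stage group. Use the same form for response in 16.6.2.1. Keep the crude chi-square test and score intervals as a sensitivity analysis for both.

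Align the wording of the decision rule in 16.5.1.1. In 16.5.4, say that the sample size was calculated with the unstratified chi-square test as an approximation.

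The cost is about one sentence in each of these four sections. Both factors are already recorded at registration (6.2.2), so no data collection changes and the sample size stays at 102 evaluable patients. The price is up to about 1 point of power if neither factor is prognostic. The change should be made before outcome data are seen.
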